## 2. Experimental Design

This investigation is an interventional and monocentric study conducted at the Grenoble Alpes University Hospital on 15 healthy volunteers. 

### 2.1. Inclusion Criteria

To be eligible for inclusion in this study, participants must meet the following criteria: (1) be aged between 18 and 65 years; (2) have a BMI higher than 20 and lower than 30; (3) be affiliated to a social security system; (4) be able to understand the study and all the associate instructions; (5) must have a transit time evaluated from 1 to 3 faeces per day (evaluated during the inclusion visit); (6) accept to maintain the same lifestyle (sport and diet) during the study duration; (7) stay in the Isère (French department) during the faeces collection time (around 96 h); (8) must have signed the study’s informed consent and collection consent. 

### 2.2. Exclusion Criteria

Exclusion criteria for this study includes the following: (1) subjects taking medication (except oral contraception) and/or probiotics and related products, (2) subjects with a known food allergy, (3) subjects who have had an intestinal obstruction, (4) subjects with inflammatory disease of the digestive tract and/or history of digestive surgery. More exclusion criteria are described in Supplementary Table S1.

### 2.3. Participants and Recruitment

Both male and female volunteers who live in Grenoble and its surrounding areas will be recruited. The participant recruitment started in October 2022 and will be completed in December 2023.

### 2.4. Data Collection

Pre-analytical assessments will be performed inside the Biology and Pathology Institute of the Grenoble Alpes University Hospital. Metabolomic, metagenomic, and culturomics analyses of the module contents will be performed as follows: the metagenomics analysis will be performed by ADM biopolis (Valencia, Spain), the metabolomics analysis by GExiM (Grenoble, France), and the culturomics analysis by the TIMC lab (Grenoble, France).

### 2.5. Clinical Study Protocol

During the screening visit, which takes place about a week before the inclusion visit at the hepato-gastroenterology department, the investigator informs the volunteer and answers any questions about the objective, the nature of the constraints, the foreseeable risks, and the expected benefits of the study. The investigator also explains the volunteer’s rights in a clinical trial and outlines the eligibility criteria. 

After receiving this information, volunteers are given at least 24 h to consider their decision to participate in the study or not. If, after the reflection period, the volunteer does not wish to give consent, he or she simply informs the research team by telephone or e-mail.

Once included in the study, on the appointed day, the volunteer comes to the hospital in the morning after a 10 h fasting to swallow the MD with 150 mL of water under the supervision of the study gastroenterologist. For women of childbearing potential, a pregnancy test is performed to exclude a pregnancy. After ingesting the MD, the volunteer must then wait 2 h before drinking and 4 h before eating. Consequently, the volunteer collects each faeces until the clinical study assistant calls him to stop the collection once all modules have been collected. For the faeces collection, the volunteer uses a special device named Fecotainer that can be placed directly in the toilet bowl. The collected sample must only contain faecal matter (no urine or blood) to be analysed. After defecation, the fresh sample is directly placed by the volunteer in a refrigerated place, and a biological transporter collects the sample from volunteer’s house to the hospital 24/7. Depending on the delivery hour at the hospital, the sample is directly prepared (from 8 h to 18 h) or placed at +4 °C (from 18 h to 8 h). Samples must be prepared in the next 24 h after collection and must be stored at +4 °C. The volunteer keeps track of their nutrition and sensation (presence or absence of pain, etc.) during study duration on a daily basis. 

The sample preparation consists first in screening for the module in the collected faecal matter. If no module is detected, the faeces collection continues. If at least one, or all modules, are detected in the collected faecal sample, the modules are recovered. The collected modules are then washed and assessed (e.g., observed leakage), weighted (to estimate the intestinal liquid volume sampled), and the content is recovered by centrifugation, leading to a sample that is divided into a pellet (bacterial content) and supernatant (intestinal metabolites). The supernatant is transferred into a new Eppendorf tube for metabolomic analysis, and its pH is measured using a pH paper indicator. The pellet is used for metagenomic analysis. For each volunteer, one module is used for multi-omics analysis, and the remaining ones (if any) are stored in the biological collection in case of a complementary analysis and as backup. If a module is contaminated by faecal matter due to leakage, the back-up module is used for the multi-omics analysis. Faecal samples are also collected from healthy volunteers and will be analysed by the same approaches as the intestinal content collected with the medical device. All samples are stored at −80 °C until analysis. 

For two volunteers, culturomics analysis will be performed if at least two out of the three modules per healthy volunteer are recovered and contain more than 50 µL, displaying no faecal contamination. The first retrieved module will be used for metagenomics and metabolomics analysis, and the second retrieved module will be used for culturomics analysis and will be directly placed in an anaerobic bag to preserve strictly anaerobic bacteria. The samples will be rapidly sent to the culturomics platform at +4 °C. In case the third module is contamination-free, it will serve as a back-up for analysis. 

The design of the study is illustrated in Figure 1.

### 2.6. Multi-Omics Analysis

Three meta-omics analysis will be performed during this clinical study (Figure 2). All samples will be analysed simultaneously and at the end of the study to avoid batch-related analysis biases, expect for culturomics. 

Metagenomics will be performed on one (small intestinal content (bacterial pellet obtained by centrifugation) + corresponding faeces) sample for each of the 15 healthy volunteers using 16S rRNA gene sequencing to determine the microbial composition of each sample. DNA from each sample will be extracted using Qiagen powerfecal pro Kits. Each sample will be amplified through PCR using a specific combination of primers specially designed and adapted for massive sequencing that allows us to capture the hypervariable region V3-V4 of the bacterial 16s rRNA [43]. To be able to construct the bacterial profile, each PCR product will be individually labelled. Each labelled product will pass through a primer-dimer removal protocol in order to allow us to increase the sequencing throughput. Once the PCR products are cleaned, they will be equimolarly pooled. The absolute abundance of 16S rDNA copy numbers representing bacterial biomass for each sample will be determined using qPCR.

Metabolomics will be performed on one (small intestinal content (liquid phase obtained by centrifugation) + corresponding faeces) sample for each of the 15 healthy volunteers. Small intestinal content samples collected by the MD and faecal matter will be analysed using liquid chromatography (Vanquish Flex, Thermo Fisher Scientific, Waltham, MA, USA) coupled with tandem Q Exactive Plus Orbitrap mass spectrometer (Thermo Fisher Scientific, Waltham, MA, USA) (LC-MS/MS). Untargeted and semi-targeted metabolomics will be performed in both positive and negative ionisation modes to characterise the metabolome of each sample. The main goal is to verify whether the volume collected by one module is sufficient to measure its metabolic fingerprint and to look for any differences with faecal matter. Principal component analysis on the metabolic fingerprints will allow us to conclude on this matrix difference. The semi-targeted approach will allow us to compare the relative amounts of approximately 45 preselected metabolites of interest between the small intestinal content and faeces.

Culturomics will be performed on two samples collected by the MD from two different healthy volunteers. For this, the small intestinal liquid recovered from the module will be diluted ten times in anaerobic phosphate-buffered saline (PBS) before being directly inoculated on Columbia +5% blood sheep agar or Yeast Casitone Fatty Acids (YCFA-modified agar in serial dilutions. Alternatively, the small intestinal liquid will be mixed with two liquid media (blood bottle enriched with rumen fluid and sheep blood, and YCFA medium enriched with rumen fluid and sheep blood) under anaerobic conditions. The same media and dilution series will also be cultivated under aerobic conditions. The incubation of cultures will be performed for a total of 10 days, with subcultures at 3 h, 6 h, 9 h, 24 h, 72 h, 7 days, and 10 days from the initially incubated liquid media (blood bottle enriched with rumen fluid and sheep blood, and YCFA medium enriched with rumen fluid and sheep blood). MALDI-TOF mass spectrometry will be carried out to identify bacteria after colony isolation. Species identified through MALDI-TOF will be confirmed via the sequencing of their 16S DNA genes. Isolates that will not be identified through MALDI-TOF will be analysed using full-length 16S rRNA gene sequencing. Strains will be banked and stored at −80 °C.

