## Abstract

The connection between imbalances in the human gut microbiota, known as dysbiosis, and various diseases has been well established. Current techniques for sampling the small intestine are both invasive for patients and costly for healthcare facilities. Most studies on human gut microbiome are conducted using faecal samples, which do not accurately represent the microbiome in the upper intestinal tract. A pilot clinical investigation, registered as NCT05477069 and sponsored by the Grenoble Alpes University Hospital, is currently underway to evaluate a novel ingestible medical device (MD) designed for collecting small intestinal liquids by Pelican Health. This study is interventional and monocentric, involving 15 healthy volunteers. The primary objective of the study is to establish the safety and the performance of the MD when used on healthy volunteers. Secondary objectives include assessing the device’s performance and demonstrating the difference between the retrieved sample from the MD and the corresponding faecal sample. Multi-omics analysis will be performed, including metagenomics, metabolomics, and culturomics. We anticipate that the MD will prove to be safe without any reported adverse effects, and we collected samples suitable for the proposed omics analyses in order to demonstrate the functionality of the MD and the clinical potential of the intestinal content.

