### 1.3. Aims and Objectives

The primary objective of this clinical study is to demonstrate the safety and performance of the medical device. This objective is, thus, composite and will be achieved if both the safety and the performance of the MD are observed for at least 12 out of 15 volunteers. 

Each volunteer will ingest only one pill (the MD) containing tree modules.

The secondary objectives of this study are as follows: (1) to verify the safety of use of the MD for the collection of intestinal content, (2) to verify that the MD is transiting in the human intestinal tract, (3) to evaluate the capture of intestinal liquid by the MD, (4) to verify that the MD opened in the intestine, (5) to verify the state of the MD after collection, (6) to evaluate the sample’s functional potential and identify biomarkers (microorganisms, metabolites) via metagenomics and metabolomics, (7) to estimate the volunteer’s experiences about the MD ingestion and its use, and (8) to obtain the sample’s functional potential and identify biomarkers via culturomics for two subjects.

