### 2.8. Statistical Analysis

Categorical variables will be presented using counts and frequencies, while continuous variables will be presented using mean, standard deviation, median, and interquartile range. Statistical significance will be declared when *p* < 0.05, without adjustment for multiple testing. Any comparisons between groups will be made using non-parametric tests, given the small sample size: Fisher’s tests for qualitative variables and Wilcoxon’s tests for quantitative data. Analyses will be performed using R (version ≥4.2). The normality of continuous variables will be assessed graphically. No replacements of missing data will be performed.

The main objective of the study will be achieved if the safety and performance sub-criteria are met for at least 12 out of the 15 volunteers. All secondary objectives will be analysed using descriptive tools except multi-omics analyses. 

A security interim analysis will be performed after the inclusion of the 3rd volunteer. This will focus strictly on the safety component of the primary outcome. No adjustments for alpha risk inflation are planned.

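### For the untargeted metabolic fingerprint, the conclusion on module content versus faeces is attached to principal component analysis, which is descriptive, ignores the pairing and carries no decision rule

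*Protocol article*

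**What the plan says.** Section 2.6 (Multi-Omics Analysis) plans one module sample and the corresponding faeces from each of the 15 volunteers, both analysed by LC-MS/MS. It states two aims for the metabolomics: to check that one module yields enough volume for a metabolic fingerprint, and "to look for any differences with faecal matter". It then names the method for the second aim: "Principal component analysis on the metabolic fingerprints will allow us to conclude on this matrix difference". Separately, a semi-targeted analysis is to "compare the relative amounts of approximately 45 preselected metabolites of interest between the small intestinal content and faeces".

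The Abstract lists among the secondary objectives "demonstrating the difference between the retrieved sample from the MD and the corresponding faecal sample". The numbered list in section 1.3 has no explicit comparison with faeces. Its nearest item is "to evaluate the sample’s functional potential and identify biomarkers (microorganisms, metabolites) via metagenomics and metabolomics".

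Section 2.8 (Statistical Analysis) says "Any comparisons between groups will be made using non-parametric tests, given the small sample size", naming Fisher's test for qualitative and Wilcoxon's test for quantitative variables. It adds "Statistical significance will be declared when *p* < 0.05, without adjustment for multiple testing", and "All secondary objectives will be analysed using descriptive tools except multi-omics analyses".

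**The concern.** The article does not leave the method for the fingerprint open. It names one and says a conclusion will follow from it. PCA finds the directions of largest variance among all samples. It is not told which samples are module content and which are stool, nor which two come from the same person. It returns scores and loadings, and without an added rule these do not say when the two sample types differ.

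Two errors become possible. Large differences between people can fill the leading components and hide a consistent within-person shift. Conversely, if several components may be inspected, one of them may appear to separate the sample types by chance. Since section 2.8 exempts multi-omics from the descriptive-only rule for secondary objectives, some inference seems intended here, yet the tool named for the fingerprint is a descriptive one.

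**Working it through.** **No figure to reproduce.** The article gives no effect size, power or error rate for this comparison, and section 2.7 sets 15 volunteers on feasibility grounds. The check is therefore whether PCA can carry the conclusion, and whether a paired test is possible at this size.

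**1. Which method answers which question.**

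| Comparison (section 2.6) | Method named | Tests the whole profile? |
|---|---|---|
| Untargeted fingerprint | PCA | No; no rule attached |
| About 45 preselected metabolites | Not named there; Wilcoxon under section 2.8 can apply | No; one metabolite at a time |
| 16S composition | Not tied to PCA | Outside this point |

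**2. False separation (illustrative, all inputs assumed).** 1,000 runs; 15 pairs; 500 features; residual SD 1; no difference between sample types; between-person SD 0 or 1. A paired Wilcoxon test at 0.05 was applied to the component scores. Share of runs with at least one significant component:

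| Components read | Between-person SD 0 | Between-person SD 1 |
|---|---|---|
| First only | 4.3% | 4.8% |
| First or second | 9.7% | 10.4% |
| Any of first five | 22.1% | 24.3% |

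Even with a formal test added to the scores, the error rate depends on how many components may be read, and the article does not fix that number.

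**3. Hidden difference (illustrative, all inputs assumed).** 300 runs; 15 pairs; 500 features; residual SD 1; a true shift of 0.5 SD in 100 features. Separation was counted when the best cut-off on the first or second component classified at least 80% of the samples correctly. The comparator was a within-pair sign-flip test on the squared length of the mean difference vector.

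| Between-person variation | PCA separates | Paired test rejects at 0.05 |
|---|---|---|
| None | 93% | 100% |
| Five latent factors, SD 1 | 0% | 100% |

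With the shift set to zero, the paired test rejected in about 5% of runs in both settings. In this example, what PCA shows depends on between-person variation, which pairing removes.

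**4. Is a paired global test possible with 15 pairs?** Each volunteer's two labels can be swapped or not, which gives 2^15 = 32,768 arrangements. Swapping all pairs at once leaves a distance-based statistic unchanged, so the smallest attainable p is 2 / 32,768 = 0.000061. If only 12 pairs were usable (an assumption; section 2.7 plans replacement up to 15), there are 2^12 = 4,096 arrangements and the smallest p is 2 / 4,096 = 0.00049. Either is far below 0.05.

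**The case against.** The strongest reply is that this is a condensed article on a feasibility-sized pilot. The distance measure, scaling and permutation scheme of a multivariate test commonly belong in the full protocol or analysis plan, and their absence here is no fault. That stands. It does not cover a sentence that names a method and attaches a conclusion to it.

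A second reply is that the article does have tests and an alpha: section 2.8 assigns Wilcoxon and Fisher tests at 0.05 to any group comparison. That also stands, and it can serve the roughly 45 metabolites. Those tests are univariate, however, and are not linked to the PCA.

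Third, a very large difference between intestinal liquid and stool would probably show on the first component anyway. That is plausible, and it limits the practical harm. The simulations above rest on assumed inputs and show what can happen, not what will.

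A reader might also infer that the whole secondary objective rests on looking at a plot. The text does not support this. The PCA sentence covers only the metabolic fingerprint, it does not mention a plot or visual reading, and the objective of demonstrating a difference is explicit only in the Abstract. Nor should a reader infer that the article equates separation with anatomical site: it speaks of a matrix difference, which already describes a difference between sample types.

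**Conclusion.** The point holds for one analysis. For the untargeted fingerprint, the article attaches a conclusion to a descriptive method that ignores the pairing and has no error rate, and no other test it names addresses the whole profile. The size of the error cannot be derived from the article. Under the assumed null model, the false-positive rate ranged from 4 to 5% up to 22 to 24%, according to the number of components read. The verdict rests on reading the section 2.6 sentence as the stated basis for the conclusion. An analysis plan that is not shown may already hold a formal test, in which case only the wording needs correcting. The 16S comparison, the comparison of about 45 metabolites and the primary endpoint are untouched. Severity is minor to moderate.

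**What to change.** Keep PCA as a descriptive display. Replace the concluding sentence in section 2.6 with one prespecified global paired test on the fingerprint, for example PERMANOVA on Euclidean distances of log-scaled features, with permutations restricted within volunteer, reporting R2 and p. Positive and negative ionisation modes are both acquired, so state in advance how they enter that single test. If no test is added, describe the PCA result as exploratory and remove the claim that it permits a conclusion.

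The cost is a sentence or two in the plan and a few lines of R. No further samples, assays or volunteers are needed.

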### 2.7. Sample Size

The number of subjects to be included is set at 15 healthy volunteers to meet practical feasibility requirements. Any patient whose data are deemed unusable, notably due to sample transport lasting >4 h, will be replaced to obtain 15 usable samples, up to a limit of 20 patients in total.

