### 1.4. Primary Outcomes

Safety will be assessed in a binary manner as the absence of the occurrence of adverse events of grade ≥3 with a proven or reasonably conceivable causal relationship with the MD or its related procedure. Grades will be determined using the common terminology criteria for adverse events (CTCAE) classification version 5 (or 6 if available) [41]. 

Performance will be considered satisfactory if at least one of the three modules is analysable. A module will be considered analysable if (1) it is found in the faeces within a 96-h period, (2) the recovered volume of its contents is ≥25 µL, and (3) its visual condition is satisfactory (no faecal contamination).

The criteria to evaluate the secondary objectives are as follows: (1) the number and grade of adverse events notified (including response to follow-up volunteer-diaries, number of unscheduled medical visits); (2) the number of modules recovered per volunteer; (3) the volume recovered from each module (recovered volume must be ≥25 μL); (4) the pH of the recovered MD contents (a measured pH ≥5 will prove that the MD did not sample stomachal liquid where the pH is lower [42]); (5) the visual assessment of the module evaluating whether it is intact and has no visible cracks or damages that could lead to faecal contamination; (6) metabolomic and metagenomic analyses of the module contents; (7) the rating of the device (devices “acceptability”) based on the questionnaire and the end-of-participation visit with the principal investigator; and (8) the results of the culturomic analysis of the module contents, on up to two volunteers.

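### The open-ended replacement rule can take device failures, and the safety results of replaced volunteers, out of the 12-of-15 primary denominator

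*Protocol article*

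**What the plan says.** The size of the trial rests on feasibility (section 2.7): "The number of subjects to be included is set at 15 healthy volunteers to meet practical feasibility requirements". No reference success rate, error rate or power is attached to it. The same section gives the replacement rule: "Any patient whose data are deemed unusable, notably due to sample transport lasting >4 h, will be replaced to obtain 15 usable samples". Total enrolment is capped at 20.

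Section 2.8 says that the main objective is "achieved if the safety and performance sub-criteria are met for at least 12 out of the 15 volunteers". Section 1.3 sets the same threshold.

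Section 1.4 defines the two components per volunteer. Safety is the absence of a device- or procedure-related adverse event of grade 3 or higher. For performance: "Performance will be considered satisfactory if at least one of the three modules is analysable". A module is analysable if "it is found in the faeces within a 96-h period", if at least 25 µL is recovered from it, and if its visual condition is satisfactory, without faecal contamination.

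Section 2.6 plans the metagenomic and metabolomic analyses on one intestinal sample, with the matching faeces, from each of the 15 volunteers.

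**The concern.** The replacement rule and the success rule use the same 15, and the boundary between them is not drawn. Data can be deemed unusable for reasons other than slow transport, and none is listed or excluded. A volunteer with no module found, too little volume or only contaminated modules has plainly not supplied a usable intestinal sample. That volunteer is also exactly the failure that the performance endpoint is meant to count. The article does not say that such volunteers may not be replaced, when the decision is taken, or whether a replaced volunteer stays in the denominator.

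Safety is affected too. It does not depend on whether a sample is usable, and a replaced volunteer has still swallowed the device. If the 15 are those left after replacement, that person's safety result drops out of the primary count, even when the reason for replacement was purely logistic.

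At stake is the trial's only success criterion. If the denominator can be selected on the outcome, the observed proportion is biased upwards and 12 of 15 no longer means 80% of those exposed.

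**Working it through.** **Inputs from the article.** Target 15 and cap 20, so at most 20 − 15 = 5 replacements (section 2.7); success at 12 or more of 15 (sections 1.3 and 2.8). The sample size has no calculation behind it, so there is no figure to reproduce.

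**Assumptions, not in the article.** The true chance *p* that a volunteer meets both sub-criteria, and the share *f* of failing volunteers who are replaced. Both are shown over a range.

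**Step 1: fixed 15, no replacement.** P(pass) = Σ C(15,k) p^k (1−p)^(15−k), for k = 12 to 15.

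**Step 2: every failure replaced until the cap (f = 1).** With eight failures among 20 enrolled, five can be replaced and three remain, which leaves 12 successes in a final set of 15. The rule is then met exactly when at least 12 of 20 would succeed: P(pass) = Σ C(20,k) p^k (1−p)^(20−k), for k = 12 to 20.

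**Step 3: half the failures replaced (f = 0.5).** Exact recursion over volunteers. A success adds one counted volunteer and one success; a failure is replaced with probability f and otherwise counted. It stops at 15 counted or 20 enrolled. If the cap comes first, the rule is still taken as at least 12 successes.

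| p | Fixed 15 | Half replaced | All replaced |
|---|---|---|---|
| 0.5 | 0.018 | 0.152 | 0.252 |
| 0.6 | 0.091 | 0.409 | 0.596 |
| 0.7 | 0.297 | 0.715 | 0.887 |
| 0.8 | 0.648 | 0.922 | 0.990 |

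At p = 0.9 the fixed-15 value is already 0.944, and full replacement takes it to 1.000.

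**Step 4: replacement only for transport, unrelated to device success.** The same recursion, with an assumed 10% transport loss, gives 0.090, 0.295 and 0.645 at p = 0.6, 0.7 and 0.8, against 0.091, 0.297 and 0.648 without loss. At an assumed 20% loss the values fall to 0.078, 0.260 and 0.584, because the cap is sometimes reached before 15 are counted. Replacement of this kind does not inflate the chance of success.

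**Step 5: what could be reported.** Under step 2, the least favourable passing result is 12/20 = 60% of those who swallowed the device (Clopper-Pearson 95% CI 36% to 81%). It would appear as 12/15 = 80% (CI 52% to 96%). If 15 usable samples were reached with five failures replaced, performance would read 15/15, against 15/20 = 75% (CI 51% to 91%) among those exposed.

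**The case against.** The article nowhere says that device failures will be replaced. Its one named reason is logistic, and it uses a separate term, analysable, for device performance. A threshold that tolerates three failures makes most sense if failures stay among the 15. All of this is fair: replacement of device failures is a permitted reading, not a stated rule. Section 2.6, however, points the other way, since it expects an intestinal sample from each of the 15. The text does not settle the matter.

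The figures in the last column also depend on a convention at the cap that the article does not state. If success required 15 usable samples to be reached, P(at least 15 of 20) would be 0.021, 0.126 and 0.416 at p = 0.5, 0.6 and 0.7. That is still above the fixed-15 values, but far less so.

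It can be said that analysis sets belong in the full protocol or the SAP. That would excuse silence. Here the article states both the replacement rule and the success rule, and the difficulty comes from reading them together.

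Two stronger readings should be resisted. Section 2.5 says "The collected sample must only contain faecal matter (no urine or blood) to be analysed", and a reader might infer that a volunteer with a bleed would be classed as unusable and lost from the safety count. That sentence is a requirement on each collected stool. It does not make a volunteer unusable, and section 1.4 lists the number and grade of notified adverse events as a secondary criterion. A reader might also infer that slow transport harms only the omics results. The article does not say so: modules are assessed at the hospital after transport, and the effect of delay on volume or visual condition is not described.

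**Conclusion.** The concern holds in a bounded form. The replacement criterion is open-ended, it overlaps the performance endpoint, and the denominator of the 12-of-15 rule is not tied to those who swallowed the device. Device failures, and the safety results of replaced volunteers, can therefore leave the primary analysis.

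The possible effect is large. At an assumed true success rate of 0.7, the chance of meeting the rule goes from 0.30 to 0.71 if half the failures are replaced and to 0.89 if all are. These figures rest on assumed values of p and f and on the stated convention at the cap. If replacement is purely logistic and unrelated to the device, there is almost no effect on the chance of passing, and only the safety denominator remains at issue.

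A reader might conclude that the objective is close to self-fulfilling. The numbers do not support that in general: even with every failure replaced up to the cap, the rule would still be missed about 75% of the time at p = 0.5 and 40% at p = 0.6. The point still needs correcting before analysis, because it decides what the headline result can mean.

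**What to change.** Amend sections 2.7 and 2.8, and the SAP to match:

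- Define unusable, and limit replacement to prespecified logistic reasons unrelated to the device, such as transport over 4 h. Take the decision before the modules are inspected.
- State that non-recovery within 96 h, less than 25 µL and faecal contamination are never grounds for replacement, and that a volunteer left without an analysable module for these reasons counts as a performance failure in the 12-of-15 rule.
- Analyse safety in everyone who swallowed the device, up to 20.
- List every replacement with its reason, and also report the composite over all who swallowed the device with an exact confidence interval.

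This costs wording only, with no added volunteers or procedures. The downside is that the reported success proportion may be less favourable.
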